**Fig. 2 Fig2:**

The total study period and the evaluation time points

### Data collection and management

The research staff is responsible for the collection of baseline characteristic data and the allergen test results during the screening period. The baseline variables will include: center location, age, gender, highest education level achieved, employment, diagnosis, nasal mucosal examination result, allergen examination result, typical symptoms, occurrence time of symptoms, time of recurrence or aggravation, accessory examination of nasal mucosa and nasal sinus, family history, relevant diseases (allergic asthma, allergic conjunctivitis), other relevant clinical disorders (such as hypertension, diabetes, and cardiac arrhythmia), as well as the questionnaires such as the TNSS, the TNNSS, and the RQLQ.

Participants are required to record in the daily diary the symptoms of AR and intake of any other medications during this study period. Outcome evaluators will examine the outcomes at baseline, 2 weeks (within treatment), 4 weeks (end of treatment), 3 months (within follow-up), and 6 months (end of follow-up). Data on nasal symptoms, non-nasal symptoms, and patients’ quality of life will be collected.

Data monitoring and management will be performed by the Clinical Evaluation Center of CACMS every 3 months. Two assistants will enter all data into an electronic database by double data entry. The statistical manager will be responsible for source data organizing, coding, range checking for data values and converting data to ensure data quality.

### Statistical analysis

#### Sample size calculation

The sample size calculation was performed with SAS 9.3 software (SAS Institute Inc., Cary, NC, USA) in the Clinical Evaluation Center of CACMS. The mean change in TNSS before and after treatment was used as the indicator for the efficacy evaluation in the calculation of the sample size. Results from our previous studies showed that the mean TNSS change was 4.90 ± 3.54 after acupuncture treatment [27] and 3.4 ± 1.0 after loratadine treatment [28]. Thus, we performed a non-inferiority test to calculate the appropriate trial sample size with 80 % power, alpha of 0.05, and an acceptable delta of 0.2. The results showed that a clinically important difference can be detected by a sample size of at least 39 in each group. This number was then increased to 49 per group (total of 98) to allow for a predicted 20-% dropout rate.

#### Statistical methods

The statistical analysis will be performed with SPSS 17.0 software (SPSS Inc., Chicago, IL, USA) in the Clinical Evaluation Center of CACMS. We will perform baseline adjusted analyses for the following variables (the center and severity), and the baseline value of the corresponding outcomes will be assessed. The data analyses will be conducted on an intention-to-treat population. Descriptive statistics will be used to compare the baseline measures and patients’ characteristics between the two groups. Regarding the primary and secondary outcome measures, the two-sample *t* test or Wilcoxon rank sum test will be used to compare the differences between the two groups from baseline to the end of treatment (*p* < .05 will be considered statistically significant). If an imbalance occurs in baseline characteristics between the two groups, ANCOVA will be applied.

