## Methods

### Study design

The trial is designed as multicenter, parallel-group, randomized, single-blinded (outcome assessors), non-inferiority trial, comparing the differences between warm needling therapy and loratadine for PAR.

We will recruit 98 patients with PAR from three hospitals in China. According to their group assignment, patients will receive either 12 sessions of warm needling or the oral medication loratadine for 4 weeks.

The study design flowchart is presented in Fig. 1, and the study design schedule is shown in Table 1.

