#### Follow-up

Upon completion of the 4-week treatment period, there is a further 6-month follow-up period. The research staff will continue to follow the participants via telephone communication and short messaging service (SMS). The frequency of follow-up is monthly and we will keep a record of the assessment of symptoms and medication compliance or changes. In the event of participants discontinuing or deviating from intervention protocols, the study staff will record the reasons for this and their medications and then exclude the participants from the study, and the latest outcome data including symptoms and frequency of the attacks.

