#### Missing data and sensitivity analysis

The data used in the main statistical analysis should be collected in the fourth week of the treatment and at the half-year follow-up. In order to avoid missing data, we will provide an economic compensation for participants who have finished the trial and provided the completed data. The investigators have a wealth of experience in managing patients and collecting data in previous trials. They record the contact information of participants and keep in touch with them through a variety of means during the treatment and follow-up periods.

If the data are not obtained, we will record the time and reason for the missing data and will analyze the assumed missing data mechanism. For these missing data, we will use the multiple imputation adjustment approach. After the main analysis, we will perform a sensitivity analysis for the various datasets to enable us to judge the impact of missing data on our results.

A fully specified statistical analysis plan will be written independently.

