#### Publications and dissemination

After completing data analysis, publications will be planned in Chinese and English versions. Regardless of the findings, we plan to disseminate all of the trial results in conferences or publications.

All of the staff who participated in the organization, implementation, data management and data statistical analysis will be affirmed in the authorship and we do not intend to use any professional writers.

There is no plan to allow public access to the full protocol, participant dataset, or statistical code. But, if necessary, individuals can gain access to the full protocol through the Ethics Committee of the Institute of Acupuncture and Moxibustion of CACMS.

This protocol was written following the Standard Protocol Items: Recommendations for Interventional trials (SPIRIT) checklist (see Additional file 1). The future report will follow the Consolidated Standards of Reporting Trials (CONSORT) guidelines [29], Revised Standards for Reporting Interventions in Clinical Trials of Acupuncture [30], and the extension of CONSORT for reporting non-inferiority randomized trials [31].

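### Participants who stop or deviate are to be excluded from the study, which conflicts with the promised intention-to-treat analysis of a month-6 outcome

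*Protocol article*

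**What the plan says.** All references are to the protocol article.

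- **Design.** Study design describes a "single-blinded (outcome assessors), non-inferiority trial".
- **Population.** Statistical methods names one population for all analyses: "The data analyses will be conducted on an intention-to-treat population".
- **Primary outcome.** Primary outcome measure sets the endpoint as the change in TNSS from baseline to 6 months after treatment.
- **Participants who discontinue or deviate.** Follow-up says that staff will "record the reasons for this and their medications and then exclude the participants from the study". The sentence ends with an incomplete reference to the latest outcome data, including symptoms and attack frequency.
- **Missing data.** Missing data and sensitivity analysis provides multiple imputation, then says "we will perform a sensitivity analysis for the various datasets to enable us to judge the impact of missing data on our results". It closes with: "A fully specified statistical analysis plan will be written independently".
- **Deviations are foreseen.** Concomitant care and intervention prohibits several drug classes, allows intranasal steroids for severe symptoms and has that use recorded for analysis. Discontinuation of the intervention lists the circumstances that end treatment. It speaks of ending the intervention, not of ending outcome assessment.

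**The concern.** Intention-to-treat means that everyone randomised is analysed in the assigned group, whatever treatment they went on to receive. That requires outcome data on people who stopped or deviated. The Follow-up section removes those same people from the study, possibly months before the primary assessment. The two instructions cannot both be carried out in full.

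What is at stake is the primary result. Whether someone stops or turns to other medication probably depends on their symptoms, so those removed are unlikely to resemble those who stay. Patients and operators are not blinded, so the reasons for leaving may also differ between a course of needling and a daily tablet. If these people are dropped, the comparison is no longer between the randomised groups, and it is not a defined per-protocol comparison either. If they are imputed, the month-6 values come largely from participants who remained.

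**Working it through.** **Step 1. The instructions side by side.** Take a participant who stops treatment in week 3.

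- Under Follow-up: reasons and medications are recorded, the participant is excluded, and the latest outcome data are what remains.
- Under Primary outcome measure: a month-6 TNSS is needed.
- Under Statistical methods: the participant belongs in the analysis.
- Under Missing data and sensitivity analysis: the month-6 value is imputed.

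The value is missing because the protocol stopped looking for it, not because it was unobtainable.

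**Step 2. The plan's own sample size.** Inputs from Sample size calculation: changes of 4.90 (SD 3.54) and 3.4 (SD 1.0), delta 0.2, alpha 0.05, power 80%, dropout 20%. Assumptions: delta is in TNSS points, and alpha is one-sided 0.025.

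- n per group = (3.54² + 1.0²) × (1.96 + 0.842)² / (1.5 + 0.2)² = 13.53 × 7.85 / 2.89 = 36.8, so 37. A t-based calculation gives 38. The article states 39.
- The same calculation at one-sided 0.05 gives 29 (30 with t), further from 39.
- Dropout: 39 / 0.8 = 48.75, so 49 per group, as stated.

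**Step 3. How far exclusion could move the result.** Suppose a share m of one arm is excluded, and their true mean change at month 6 differs by D from what is imputed for them. That arm's mean is then wrong by m × D, and the bias in the comparison is the net of the two arms' errors. The net D that produces a bias of 0.2 is 0.2 / m. The documents give no m, so 10% to 30% is an assumption.

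| Share excluded, one arm | D giving a bias of 0.2 |
|---|---|
| 10% | 2.0 points |
| 20% | 1.0 point |
| 30% | 0.67 point |

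The sign depends on which arm loses more people and on whether those people did better or worse than imputed. Equal errors in both arms cancel.

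For scale, the standard error is √(13.53/39) = 0.589 at 39 per group and √(13.53/49) = 0.526 at 49. The 95% half-width at 39 is 1.96 × 0.589 = 1.15. A bias of 0.2 is therefore small beside the sampling error, but as large as the margin.

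**Step 4. Dilution, for comparison.** Let a share f of patients contribute no between-arm difference. The chance of claiming non-inferiority is Φ((0.2 + true × (1 − f)) / SE − 1.96).

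- Needling truly worse by 0.2, f = 20%: 1 − Φ(1.96 − 0.04/SE) = 2.9% at 39 per group and 3.0% at 49, against 2.5% without dilution. With one-sided 0.05, 5.0% becomes 5.7% and 5.8%.
- Needling truly worse by 0.2, f = 100%: 1 − Φ(1.96 − 0.2/SE) = 5.3% and 5.7%. This is the ceiling for dilution alone at one-sided 0.025.
- Needling truly better by 1.5, as planned, 39 per group: the chance of a claim falls from 82% to 75%, 66% and 56% at f = 10%, 20% and 30%.

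**The case against.** The Follow-up sentence is garbled. It mentions the latest outcome data, and multiple imputation is provided, so an excluded participant might stay in the analysis set with later values imputed. That stands as a possible reading, and it would keep the intention-to-treat label formally true. It does not recover the month-6 observations. Imputation can use baseline and earlier scores, which would shrink D in Step 3, but what happened after exclusion remains unobserved.

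A reader might go further and infer that naming intention-to-treat alone tilts this non-inferiority trial towards success, and that the lack of a required per-protocol analysis is an error. The documents do not support either inference. Dilution helps a claim only where needling is truly worse. Under the benefit the plan assumes, it hurts the claim, and at the margin its effect is small. Supporting populations are commonly left to the analysis plan. The article announces one, and it commits to reporting under "the extension of CONSORT for reporting non-inferiority randomized trials". Its sensitivity analyses are aimed at missing data, so they do not promise a per-protocol set, but they do not exclude one. Such a set would also not necessarily remove patients who used intranasal steroids for severe symptoms, since that use is permitted.

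**Conclusion.** Wrong as written: the Follow-up and Statistical methods sections conflict on participants who stop or deviate, and they must be reconciled. The consequence is loss of primary-outcome data on participants who are unlikely to resemble the rest, with possible bias in either direction. Its size cannot be fixed from the documents. With an assumed 20% excluded from one arm, a net unexplained difference of 1.0 point is enough to equal the margin, if delta is read as TNSS points.

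The conclusion rests on the conflict, not on error rates. Dilution taken alone moves the false-claim rate at the margin from 2.5% to about 3.0% under the 20% assumption, which would not by itself justify a change. Success in both an intention-to-treat and a per-protocol set is a common convention for non-inferiority. Its absence here is not a fault in the plan.

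**What to change.** Amend Follow-up to say, in substance: participants who stop or deviate from the assigned intervention remain in scheduled outcome assessment to month 6 unless they withdraw from it; the reasons, deviations and other medications are recorded; and all are analysed in the group to which they were randomised. Add to Missing data and sensitivity analysis that multiple imputation is kept for values that could not be obtained. This concerns data collection and analysis only. It leaves the rules on stopping treatment and on permitted medication as they are.

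Optionally, the analysis plan can define a per-protocol set before unblinding, as a supporting analysis. If per-protocol losses stay within the 20% allowance, 49 × 0.8 = 39.2 leaves about 39 per group, the calculated size. Requiring success in both sets is a suggestion.

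The cost is a small amount of extra contact, since monthly telephone and SMS follow-up already exists. Trial status says recruitment is only beginning. The change has to be made while participants can still be followed, because an analysis plan written later cannot supply scores that were never collected.

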The results from our previous international, multicenter clinical study in collaboration with South Korea revealed that 4-week long, active acupuncture treatment was significantly better at reducing AR symptoms compared with sham acupuncture and non-active treatment [13]. Furthermore, AR symptoms continued to reduce in the subsequent 4-weeks of follow-up, indicating the residual effect of acupuncture. Previous studies have demonstrated that moxibustion has a regulative effect on immune system function [14, 15]. Consequently, we have optimized the intervention scheme to warm needling. There are two types of warm needling, the one we used consists of placing an ignited moxa stick on the handle of the needle after insertion. Our hypothesis is that warm needling will achieve equal or better long-term symptom relief of AR and reduce its recurrence.

In previous studies of immunotherapy and pharmacotherapy effects on AR, the placebo control group treatment provided over 50 % symptom relief [16]. In previous clinical studies of AR treated with acupuncture therapy, placebo acupuncture was widely adopted as the control group. In this study, however, we have selected western medicine as the positive control instead of placebo acupuncture. Oral antihistamines are usually the first-line medication for AR symptom relief. Loratadine, as a second-generation antihistamine agent, has a strong selective antagonistic effect on the peripheral histamine H1 receptors, providing long-lasting effect without sedating the central nervous system. Not only is loratadine used in relieving and preventing AR-associated symptoms such as rhinorrhea, itching, sneezing, nasal blockage, and ocular symptoms [17, 18], it is also widely used in the treatment of other allergic diseases. After a detailed evaluation of the desired and the adverse effects, we chose loratadine as the intervention for the control group.

We have designed a multicenter, randomized controlled trial (RCT) for patients with PAR, using oral loratadine as control. The purpose of this trial is to answer two questions: (1) is the effect obtained by warm needling equal to or better than that achieved by loratadine? and (2) is the treatment of warm needling safe for patients with PAR?

The study was registered on ClinicalTrials.gov (NCT02339714).

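### The trial is declared and sized as non-inferiority, but the primary analysis it states is a difference test at p<.05 that never uses the 0.2 margin

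*Protocol article*

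**What the plan says.** **Design and question.** The protocol article, under Study design, reads: "The trial is designed as multicenter, parallel-group, randomized, single-blinded (outcome assessors), non-inferiority trial". The Abstract and the Discussion also call the trial non-inferiority. The first question in the Background is "is the effect obtained by warm needling equal to or better than that achieved by loratadine". Under Publications and dissemination, the authors commit to reporting under the CONSORT extension for non-inferiority trials.

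**Sizing.** Under Sample size calculation: "we performed a non-inferiority test to calculate the appropriate trial sample size", with "80 % power, alpha of 0.05" and a delta of 0.2. This is the only place where the margin appears. Neither its unit nor the sidedness of alpha is given.

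**Analysis.** Under Statistical methods, for primary and secondary outcomes, a two-sample t "test or Wilcoxon rank sum test will be used to compare the differences between the two groups", with p<.05 as the criterion. The same section mentions baseline-adjusted analyses (center, severity, baseline value of the outcome) and ANCOVA if baseline characteristics are imbalanced. It describes the comparison as running to the end of treatment, whereas Primary outcome measure sets the primary time point at 6 months after treatment.

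**Deferral.** Missing data and sensitivity analysis says that a full statistical analysis plan will be written separately. It is not available here.

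**The concern.** A t test or Wilcoxon test judged at p<.05 is, on its natural reading, a test of zero difference. Non-inferiority is a different hypothesis: that warm needling is not worse than loratadine by more than the margin. The decision needs a confidence bound, or a shifted null, that uses the margin.

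The stated analysis has three possible outcomes:

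- A significant result favouring warm needling excludes zero, so it also excludes -0.2. Non-inferiority follows.
- A significant result favouring loratadine gives no claim for warm needling.
- A non-significant result says nothing either way about the margin, and the protocol gives no rule for it.

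The third outcome matters because the question asked is whether warm needling is equal or better. With no rule fixed beforehand, the main claim could be settled after the data are seen. If the Wilcoxon test were chosen, its p value would not translate into a statement about mean TNSS points.

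**Working it through.** **Inputs** (Sample size calculation): mean TNSS change 4.90, SD 3.54 for acupuncture; 3.4, SD 1.0 for loratadine; delta 0.2; 80% power; alpha 0.05; 39 per group, raised to 49 for 20% dropout. Larger change is taken as improvement, and the difference is warm needling minus loratadine.

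**Assumptions**: delta is in TNSS points; the margin test is one-sided 0.025 (lower limit of a two-sided 95% interval); the written test is two-sided 0.05.

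**Step 1. The protocol's own figure.**
- Assumed advantage: 4.90 - 3.4 = 1.5. Distance from the margin: 1.5 + 0.2 = 1.7.
- Standard error at 39 per arm: sqrt(3.54²/39 + 1.0²/39) = 0.589.
- Welch t with about 44 degrees of freedom, noncentrality 1.7/0.589 = 2.89: power 80.6% at one-sided 0.025. At 38 per arm it is 79.5%, so 39 is the smallest size that reaches 80%.
- Dropout: 39/0.8 = 48.75, rounded up to 49. This matches.

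The figure does not identify the test uniquely. A one-sided 0.05 test of zero difference at +1.5 also has 80.6% power at 39 per arm (79.6% at 38).

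**Step 2. Power of the two rules at a true difference of +1.5.**

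| Rule | 39 per arm | 49 per arm |
|---|---|---|
| Margin test, one-sided 0.025 | 80.6% | 88.9% |
| Difference test, two-sided 0.05 | 70.2% | 80.1% |

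The rules disagree when the lower 95% limit lies between -0.2 and 0. At 39 per arm that is 80.6% - 70.2% = 10.4% of trials: the margin is met but p>.05.

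A pooled-SD calculation with normal approximation, SD = sqrt((3.54² + 1.0²)/2) = 2.601, gives 82% and 72% at 39 per arm, and 90% and 81% at 49. The contrast is the same.

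**Step 3. What p>.05 would tell us.** The 95% half-width at 39 per arm is 1.96 × 0.589 = 1.15 points (1.19 with the t quantile), nearly six times the margin. Simulated Welch tests at 39 per arm give:

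| True difference | P(p>.05) | P(lower limit > -0.2) |
|---|---|---|
| -0.2 | 94% | 2.5% |
| -0.5 | 87% | 0.7% |
| -1.0 | 62% | 0.05% |
| -1.5 | 30% | below 0.01% |

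At a deficit of 1.0 point, five times the margin, the difference test is still non-significant in about 62% of trials, while a margin test would wrongly declare non-inferiority in about 1 trial in 2,000.

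**Step 4. The other analyses named.** The baseline-adjusted analyses and the conditional ANCOVA would yield an adjusted mean difference that could be set against -0.2. The protocol plans no such comparison.

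**The case against.** **The analysis can deliver non-inferiority.** A reader might infer that it cannot support such a conclusion at all. That goes too far: a significant result favouring warm needling suffices, and on the planning assumptions this occurs in about 70% of trials at 39 per arm and 80% at 49. A t-test or ANCOVA interval could also be compared with the margin. What stands is that no such comparison is stated and that a non-significant result has no rule.

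**The power contrast depends on sidedness.** A reader might infer that the size shows the 80% power to belong to a different test from the one planned. The protocol does say that a non-inferiority test was used, but 39 per arm fits a one-sided 0.05 test of zero difference equally well. The 81% and 70% figures are therefore conditional on the stated assumption.

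**Misreading p>.05 is not in the text.** A reader might infer that the authors will take non-significance as equality. No passage says so. Nor is a null hypothesis written out; zero difference is the natural reading. The 62% figure shows how little p>.05 would mean, not an error already made.

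**The rule may be in the unseen analysis plan.** That plan and the CONSORT commitment may well bring in a margin rule, so it cannot be said that non-inferiority will go untested. This does not remove the point. The protocol is not silent: it states a test and a threshold for the primary outcome that do not match its declared design. An analysis plan that follows it inherits the mismatch, and one that adds a margin rule departs from the published text.

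**Conclusion.** Wrong as written, in a limited sense. The declared design and the sizing are non-inferiority, and the stated primary analysis (t or Wilcoxon, with ANCOVA under imbalance) does not use the margin. Non-inferiority would follow only indirectly, from a significant result in favour of warm needling; any non-significant result would leave the trial's first question open.

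On the protocol's SDs, 39 evaluable per arm, delta in TNSS points and the sidedness assumed above, relying on the written test costs about 10 percentage points of power at the assumed advantage (81% against 70%), and p>.05 would remain common (about 62%) even with warm needling 1.0 point worse. The mismatch itself rests on the text alone and does not depend on these assumptions; only its size does.

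**What to change.** Rewrite the primary-analysis rule in Statistical methods, and carry it into the analysis plan:

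- Estimate the difference in mean TNSS change from baseline to 6 months after treatment (the primary time point, not the end of treatment), warm needling minus loratadine, preferably from the baseline-adjusted model, with a two-sided 95% confidence interval.
- Declare non-inferiority only if the lower limit exceeds -0.2. Before fixing this, confirm that delta is in TNSS points and state the sidedness of alpha.
- If non-inferiority is shown, declare superiority if the lower limit also exceeds 0. This fixed order needs no alpha adjustment.
- State that p>.05 is not evidence of equality.
- Keep the Wilcoxon test as a sensitivity analysis only. A per-protocol analysis is optional support.

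The cost is wording in the protocol and analysis plan, with no extra patients or data. The sample size need not change on the planning assumptions, since 39 evaluable per arm gives about 81% power for this rule at one-sided 0.025.

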**Methods/design:**

The trial is designed as a multicenter, parallel-group, randomized, single-blinded (outcome assessors), non-inferiority trial. A total of 98 patients with persistent AR will be randomly assigned into two groups. Patients in the treatment group will be treated with warm needling at GV14 and acupuncture at EX-HN3, ST2, LI20, EX-HN8, GV23, LU7, LU5 and LI4 three times a week, for a total of 4 weeks. Patients in the control group will be treated with oral loratadine 10 mg/day for 4 weeks. The primary outcome will be the change in the Total Nasal Symptom Score (TNSS) from baseline to that at 6 months after treatment during the follow-up period. The secondary outcomes will include the Total Non-nasal Symptom Score and the Rhinoconjunctivitis Quality of Life Questionnaire, changes in the TNSS from baseline to that at 2 and 4 weeks during treatment, and 3 months after treatment during the follow-up period. Outcomes will be measured at 2 and 4 weeks, and 3 and 6 months after treatment. Any side effects of treatment will be observed and recorded.

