#### Primary outcome measure

The average change in the TNSS will be measured blindly by comparing the baseline score in each group with that at 6 months after treatment during the follow-up period. The TNSS is determined in terms of the severity of rhinorrhea, nasal itching, nasal obstruction, and sneezing.

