#### Secondary outcome measures

The average change in the TNSS will be measured by comparing the baseline score in each group with that at 2 and 4 weeks during treatment, 3 months after treatment during the follow-up period. The average change in the TNNSS will be reviewed blindly by comparing the baseline score in each group with that at 2 and 4 weeks, and 3 and 6 months after treatment. The TNNSS is determined in terms of the supplementary symptoms such as post-nasal discharge, tearing, nasal or ocular itching, nasal or maxillary pain, and headache. The RQLQ will be used to observe the effect on patients’ quality of life; this will also be evaluated at 2 and 4 weeks, and 3 and 6 months after treatment.

All outcome readings will be scored on quantitative scales, and will be summarized as mean values and standard deviation.

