In the preliminary experiment, we conducted a pilot RCT with a small sample size. The purpose of this pilot study was to test the feasibility of the trial. Participants were divided into three groups and accepted warm needling on ginger, acupuncture, and loratadine separately, 20 cases in each groups. The results showed that warm needling achieved a more persistent effect than acupuncture alone and loratadine alone [27]. As a result, this multicenter RCT was designed to prove the effect of warm needling on AR. Considering the complication of manipulation of warm needling on ginger, we replaced ginger by increasing the numbers of moxa sticks. The TNSS at 6-month follow-up was taken as the primary outcome in this trial.

A previous systematic review of 13 studies showed that acupuncture was effective at reducing PAR symptoms and improving patients’ quality of life [36]. However, the duration of observation in the included studies ranged from 4 weeks to 3 months, and the time of follow-up was short, resulting in lack of adequate evaluation of the long-term efficacy of acupuncture and moxibustion. Therefore, the time of follow-up in our study will be 6 months to ensure persistent observation of the efficacy maintenance.

We expect that this study results will provide evidence to determine the effects of warm needling therapy compared to loratadine. Our final goal of this study is to evaluate differences in the short-term and long-term effects between the two therapeutic methods, especially the long-term effect of warm needling therapy.

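### The planned between-group test stops at the end of treatment (week 4), but the primary outcome is TNSS change at 6 months, and the missing-data section puts both times in the main analysis

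*Protocol article*

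**What the plan says.** Three places in the protocol article fix the primary outcome, and they agree.

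- The abstract (Methods/design): "The primary outcome will be the change in the Total Nasal Symptom Score (TNSS) from baseline to that at 6 months after treatment".
- Primary outcome measure: average TNSS change, obtained by "comparing the baseline score in each group with that at 6 months after treatment during the follow-up period".
- The main Discussion: "The TNSS at 6-month follow-up was taken as the primary outcome in this trial".

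Week-4 TNSS has its own declared place. Secondary outcome measures describes "comparing the baseline score in each group with that at 2 and 4 weeks during treatment, 3 months after treatment", and the abstract also lists it as secondary.

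The analysis text says something else. In Statistical methods the sentence that names the test opens "Regarding the primary and secondary outcome measures, the two-sample" and goes on to say that the t test or rank sum test will "compare the differences between the two groups from baseline to the end of treatment". Data collection and management labels the visits as "4 weeks (end of treatment), 3 months (within follow-up), and 6 months (end of follow-up". Finally, Missing data and sensitivity analysis states: "The data used in the main statistical analysis should be collected in the fourth week of the treatment and at the half-year follow-up".

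**The concern.** A reader who follows Statistical methods as printed would compare the arms at week 4 and stop there. The outcome that the trial declares primary would have no stated test. A reader who follows the missing-data section would treat week 4 and month 6 as together forming the main analysis, although one is primary and the other secondary.

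The choice of time changes the question. At week 4 the control arm is finishing its four-week course of loratadine. At month 6 that course ended about 6 months before, and oral antihistamines are among the medicines that the protocol prohibits during follow-up. Week 4 asks how warm needling compares with a drug while the drug is being taken; month 6 asks how long benefit lasts once both treatments have stopped. The article says that its interest lies above all in the long-term effect, so a main result taken at week 4 would not answer the question that the trial was set up to ask.

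**Working it through.** No sample-size or error-rate arithmetic applies, so the check sets the sections side by side.

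**Step 1: what each section fixes**

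| Section of the protocol article | Time point | Status given |
|---|---|---|
| Abstract; Primary outcome measure; Discussion | month 6 | primary |
| Abstract; Secondary outcome measures (TNSS) | weeks 2 and 4, month 3 | secondary |
| Statistical methods | end of treatment | test for primary and secondary outcomes |
| Missing data and sensitivity analysis | week 4 and month 6 | main statistical analysis |

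**Step 2: can the end of treatment mean month 6?** No. Data collection and management attaches that label to 4 weeks and gives month 6 a different one, the end of follow-up. The study schedule (Table 1) likewise places W4 in the treatment period and M6 in follow-up. The Follow-up section starts the 6-month period once the 4 weeks of treatment are over.

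**Step 3: what the test sentence covers if taken literally.** Three measures (TNSS, TNNSS, RQLQ) are each assessed at four times after baseline (weeks 2 and 4, months 3 and 6), which makes 3 × 4 = 12 measure-by-time comparisons. A change from baseline to the end of treatment is the week-4 comparison, so 3 of the 12 are covered. Even if the phrase is stretched to include everything up to the end of treatment, 3 × 2 = 6 are covered, and the other 6, all those at months 3 and 6, are not. The primary outcome is among those 6 on either reading.

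**Step 4: does any other section settle it?** The sample size section does not. It is based on TNSS change before and after treatment and names no 6-month point. The article announces a separate analysis plan, but that cannot reconcile two statements already printed here: its author would have to depart either from the primary outcome section or from the test sentence.

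**Result.** There are two distinct time points, week 4 and month 6. The outcome sections, the test sentence and the missing-data sentence give three incompatible accounts of their role: month 6 alone, week 4 alone, and both.

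**The case against.** The best defence is that the outcome hierarchy is clear and one analysis sentence is out of step with it. Month 6 is named primary three times, no section calls week 4 primary, and week-4 TNSS is listed as secondary. Since the literal test sentence would also leave every other follow-up comparison untested, it is probably a drafting slip and not a deliberate switch. The missing-data sentence can be read as naming the data needed for the main short-term and long-term comparisons, both of which the article gives as aims. Much of this stands. It shows what was probably meant and makes the repair easy. It does not remove the conflict, because the slip sits in the sentence that governs the primary test.

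Three stronger readings are tempting and should not be made.

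- *That the plan fixes three primary time points.* It does not: only two times are involved, and only month 6 is ever called primary.
- *That the analyst may freely report whichever time succeeds, so that the type I error is inflated by a calculable amount.* No section says that success at either time would suffice, and the article gives no correlation between the two times from which to compute such a figure. With week 4 tested alone, or with success required at both times, there would be no inflation. Choosing week 4 as the main result would also contradict the declared hierarchy.
- *That the lack of a testing order between the two times is itself a defect.* Such detail is commonly left to the analysis plan, which the article says will be written separately.

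**Conclusion.** The point holds as a contradiction in the printed text. Taken literally, the only between-group test described does not test the primary outcome, because it ends at week 4, about 6 months before that outcome is measured. The missing-data section adds to the uncertainty by placing a secondary time point beside the primary one in the main analysis.

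The conclusion rests on one reading, that the end of treatment means 4 weeks, and the article supplies that definition itself. It needs no assumption about effect sizes, correlations or error rates, and it alters no stated figure. It is wrong as written and should be corrected because it concerns the primary test, even though the intended hierarchy can be inferred.

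**What to change.** Two wording changes, both bringing the analysis text into line with the outcome sections:

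1. **Statistical methods.** State that the primary between-group comparison is TNSS change from baseline to 6 months after treatment, and that each secondary outcome is compared at the time points listed for it under Secondary outcome measures.
2. **Missing data and sensitivity analysis.** Limit the main (primary) analysis to the 6-month data and label the week-4 data as secondary.

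The separate analysis plan should carry the same statements. Making the week-4 test conditional on the month-6 result is not needed to cure the conflict.

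The cost is about two sentences, with no change to sample size, visits or conduct. Trial status says that recruitment is only beginning, so the change can be made and dated before any 6-month outcome data exist.
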